### 6.1 Name and description of investigational products

*Alitretinoin* is a retinoid drug. The pharmacological action of retinoid drugs may be explained by their effects on cell proliferation, cell differentiation, apoptosis, angiogenesis, keratinization, sebum secretion and immunomodulation. Unlike other retinoids, which are specific agonists of either RAR or RXR receptors, alitretinoin binds to members of both receptor families. The mechanism of action of alitretinoin in chronic hand eczema is unknown. It has been shown that alitretinoin has immunomodulatory and anti-inflammatory effects that are relevant to skin inflammation. CXCR3 ligands and CCL20 chemokines, that are brought to expression in eczematous skin lesions, are down-regulated by alitretinoin in cytokine stimulated keratinocytes and dermal endothelium cells. In addition, alitretinoin suppresses the expansion of cytokine activated leukocyte subsets and antigen presenting cells. It has been observed that in humans alitretinoin only minimally affects sebum secretion.(10)

*Azathioprine* is a prodrug of 6-mercaptopurine (6-MP). 6-MP is inactive in itself, but works as a purine antagonist. It requires uptake into the cell and intracellular anabolism to thioguanine-nucleotides (TGN's) for immunosuppression. The TGN's and other metabolites (e.g. 6-methylmercaptopurine nucleotides) inhibit *de novo* purinesynthesis and interconversions of purine nucleotides. The TGN's are also incorporated in nucleic acids and this contributes to the immunosuppressive action of the drug. Another potential mechanism of action for azathioprine comprises the inhibition of multiple pathways in nucleic acid biosynthesis. This impedes the initiation and accumulation of an immune response. Due to the nature of these mechanisms, azathioprine takes several weeks to months to show its therapeutic effect. (18)

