#### 8.1.2 Secondary study parameters/endpoints

##### *Severity of hand eczema*

- Between-group difference in mean change in PGA between baseline and 12 and 24 weeks.
- Between-group difference in response to treatment between baseline and 12 weeks of treatment.
- Between-group difference in mean change between baseline and week 4, 8, 12 and 24, assessed by the Hand Eczema Severity Index (HECSI) score. (21) The HECSI is an objective severity assessment based on clinical symptoms only. It includes erythema, fissures, vesicles, scaling, oedema, papules and measurement of the affected area. The score ranges from 0-360, with 360 indicating the most severe eczema.
- Between-group difference in time to response (time to first PGA improvement of  $\geq 2$  steps). This is only measured at control visits so possible outcome is limited to 4, 8, 12 and 24 weeks.

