### 10.2 Secondary study parameters

#### *Severity of hand eczema*

- Between-group difference in mean change in PGA between baseline and 12 and 24 weeks. For comparison of mean change between the alitretinoin and azathioprine group at week 12 and 24, the Student's t-test or Mann-Whitney U-test will be used, depending on distribution of data.
- Between-group difference in response to treatment between baseline and 12 weeks of treatment. For comparison of proportions in the alitretinoin and azathioprine group the chi-square test will be used.
- Between-group difference in mean change between baseline and week 4, 8, 12 and 24, assessed by the Hand Eczema Severity Index (HECSI) score. This will be described graphically. For comparison of mean change between the

alitretinoin and azathioprine group at week 12 and 24, the Student's t-test or Mann-Whitney U-test will be used, depending on distribution of data.

- Between-group difference in time to response (time to first PGA improvement of  $\geq 2$  steps). This will be analysed using a Kaplan-Meier product limit estimator. For comparison between the alitretinoin and azathioprine group the Log-rank test will be used.

*Patient rated outcome measures (PROMs):*

*Quality of life*

- Between-group mean change in quality of life between baseline and 12 and 24 weeks, assessed by the Quality Of Life in Hand Eczema Questionnaire (QOLHEQ). Clinically relevant improvement is defined as an absolute improvement of 15 points (theoretically corresponding to an improvement of  $\geq 1$  point on 50% of the questions) compared to baseline. For comparison of proportions of patients rated as having clinically relevant improvement in the alitretinoin and azathioprine group, the chi-square test will be used.

*Patient reported improvement*

- Between-group difference in patients reporting improvement as 'clear or almost clear' at week 12 and 24, assessed by Patient Global Assessment (PaGA). For comparison of proportions of patients rated as 'clear or almost clear' in the alitretinoin and azathioprine group, the chi-square test will be used.

*Safety and tolerability*

- Adverse events in both groups will be registered.

*Cost-utility and cost-effectiveness*

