### **10.3 Other study parameters**

Continuous data with normal distribution will be presented as mean  $\pm$  SD. Variables with a skewed distribution will be presented as median and range. Categorical variables will be expressed as frequencies and percentages. Confidence intervals (CIs) are expressed to a level of 95%.

To test for normal distribution of data, the data will be visually inspected, a Q-Q plot will be constructed and in case of doubt a test for normality will be used (e.g. Shapiro-Wilk test/Kolmogorov-Smirnov test).

For comparing normally distributed continuous data, we will use the Student's t-test. In variables with non-homogeneity of variance, the Welch test will be used.

For comparing non-normally distributed continuous data, the Mann-Whitney U test will be used.

For comparing categorical data the chi-square test will be used and the Fisher's exact test will be used in variables containing low numbers.

All P-values are two-sided and a P-value  $< 0,05$  is considered statistically significant. Statistical analysis will be performed using SPSS 22 (SPSS Inc, Chicago, IL, USA).

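### HECSI change is declared as a between-group endpoint at four visits, but 10.2 compares the arms at only two, by single-visit tests without baseline adjustment (a minor secondary-endpoint weakness)

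*Protocol*

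**What the plan says.** Section 8.1.2 of the protocol defines the endpoint: "Between-group difference in mean change between baseline and week 4, 8, 12 and 24, assessed by the Hand Eczema Severity Index (HECSI) score". Section 10.2 takes up the same endpoint and the same visits: "week 4, 8, 12 and 24, assessed by the Hand Eczema Severity Index (HECSI) score. This will be described graphically". The comparison that follows is narrower, for the "alitretinoin and azathioprine group at week 12 and 24, the Student's t-test or Mann-Whitney U-test will be used, depending on distribution of data".

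The study schedules (section 8.3, Tables 1 and 2) place PGA and HECSI scoring at week 0 and at weeks 4, 8, 12 and 24 in both arms, so the data for all four differences will exist.

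Three other places bear on the point:

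- Time to first PGA response is also a secondary endpoint. Section 8.1.2 says of it: "This is only measured at control visits so possible outcome is limited to 4, 8, 12 and 24 weeks". Section 10.2 adds: "For comparison between the alitretinoin and azathioprine group the Log-rank test will be used".
- Section 10.3 gives a general rule that names no visits: "For comparing normally distributed continuous data, we will use the Student's t-test". It sets two-sided 0.05 for all P-values and states no multiplicity adjustment.
- Section 10 mentions mixed models as the probable choice for handling missing data, conditional on what is assumed about the missingness.

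**The concern.** The endpoint is worded as a between-group difference at four visits, and at two of them the plan does not say how that difference is obtained. A graph shows the course of each arm. With no estimate or interval specified, it does not quantify the difference between them. The mean PGA change is handled differently: it is declared for weeks 12 and 24 and compared at weeks 12 and 24.

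The analysis at the two compared visits is also weaker than the data allow. Each test uses the change at one visit alone. It does not adjust for baseline HECSI and ignores the patient's other scores. That matters most at week 24. Section 8.4.1 withdraws patients without at least one step of PGA improvement at week 12, and section 8.6 moves withdrawn patients to care outside the study with no stated further HECSI scoring. Week-24 scores may thus be missing for reasons tied to earlier severity, which the earlier HECSI scores partly record.

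At stake is a secondary severity result that answers only half of the endpoint as written, and less precisely than it could.

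**Working it through.** **1. The plan's own figure.** The protocol gives no SD, effect size or power for HECSI. Its only sample-size figure is for the primary endpoint (section 4.4): 33% against 60% responders, two-sided 0.05, 80% power, 52 per group.

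- n = [1.96·√(2·p̄·q̄) + 0.8416·√(p₁q₁ + p₂q₂)]² / (p₂ − p₁)², with p̄ = 0.465.
- n = [1.96·√0.49755 + 0.8416·√0.4611]² / 0.27² = (1.3825 + 0.5715)² / 0.0729 = 52.4, rounded up to 53. Power at 52 is 79.7%.
- Drop-out of 10%: 52 / 0.9 = 57.8, so 58 per group and 116 in total.

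The stated figures reproduce to within one patient, and nothing in this point changes them.

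**2. Declared against compared.**

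| HECSI visit | Declared in 8.1.2 | Scored in both arms | Graph in 10.2 | Between-arm comparison in 10.2 |
|---|---|---|---|---|
| Week 4 | yes | yes | yes | none |
| Week 8 | yes | yes | yes | none |
| Week 12 | yes | yes | yes | t-test or Mann-Whitney |
| Week 24 | yes | yes | yes | t-test or Mann-Whitney |

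**3. What an interval at weeks 4 and 8 would tell.** In units of the SD of HECSI change, the 95% half-width is t(0.975, 2n − 2)·√(2/n).

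- n = 52 per arm: 1.98 × √(2/52) = 1.98 × 0.196 = 0.39 SD.
- n = 58 per arm (nobody lost yet): 1.98 × √(2/58) = 1.98 × 0.186 = 0.37 SD.

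The difference detectable with 80% power at one visit is (1.96 + 0.8416)·√(2/n), which is 0.55 SD at 52 and 0.52 SD at 58.

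**4. What baseline adjustment could gain.** Let ρ be the correlation between baseline and follow-up HECSI, and assume equal SDs at both. The variance of a change score is proportional to 2(1 − ρ), and that of a baseline-adjusted score to 1 − ρ². The ratio of adjusted to unadjusted variance is (1 + ρ)/2. The documents give no ρ. For an assumed 0.3 to 0.7 the ratio is 0.65 to 0.85, a variance reduction of 35% to 15%.

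**5. What four tests would cost.** With each test at 0.05 and independent visits, the chance of at least one false-positive HECSI result is 1 − 0.95² = 9.8% for two tests and 1 − 0.95⁴ = 18.5% for four. By simulation with equally correlated visits at an assumed 0.3 to 0.7, two tests give 9.5% to 8.3% and four give 17.4% to 13.0%. The missing visits are therefore better supplied as estimates than as two further tests.

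**The case against.** The strongest defence is that this is a stated choice. One item in 10.2 sets out the whole HECSI plan: all four visits drawn, two tested. A secondary endpoint may be described at some visits and tested at others, and fixing two test visits limits repeated testing in a plan without multiplicity control. Weeks 12 and 24 are also the visits of the PGA, QOLHEQ and PaGA comparisons. Single-visit tests are valid in themselves, and model detail is often left to an analysis plan. Most of this stands, and it makes the point minor. It does not say how the declared difference at weeks 4 and 8 is to be estimated. The general rule in 10.3 does not settle that either, because the specific HECSI text names two visits.

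A reader might go further and infer a bias. Section 6.1 says that "azathioprine takes several weeks to months to show its therapeutic effect", azathioprine is the hypothesised winner, and so the two uncompared visits would be those where alitretinoin leads. The documents do not support that reading:

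- Section 6.1 describes the onset of azathioprine only. Nowhere does the protocol predict an alitretinoin lead on HECSI at weeks 4 or 8.
- An onset of weeks to months can reach week 12, which is tested.
- Week 12/24 is the general pattern of the trial, so nothing suggests that the visits were picked to favour one arm.

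A reader might also conclude that an early difference between the arms could not be shown at all. That is wrong as well. Time to first PGA response is observed at weeks 4, 8, 12 and 24 and compared by log-rank test. The log-rank test does not replace the HECSI differences: it uses a coarser outcome (two steps on a five-grade scale, against a score from 0 to 360) and gives one result pooled over all visits. What remains is a gap in sensitivity and completeness.

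**Conclusion.** The point holds as a minor weakness of one secondary endpoint. Two of the four between-group HECSI differences declared in 8.1.2 have no planned estimate or interval in 10.2. The two that are compared use single-visit tests that leave baseline HECSI and the other collected scores unused. The mismatch itself rests on the text alone.

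The sizes are illustrative. The half-width of 0.37 to 0.39 SD assumes 58 to 52 patients per arm. The variance reduction of 15% to 35% assumes a baseline correlation of 0.7 to 0.3 and equal SDs. How many week-24 scores the week-12 rule removes cannot be derived from the documents.

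The primary analysis, the sample size and the log-rank comparison of early PGA response are unaffected. No tilt toward azathioprine is shown.

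**What to change.** In 10.2, replace the single-visit HECSI tests by one repeated-measures mixed model over weeks 4, 8, 12 and 24, with baseline HECSI, visit, arm and arm-by-visit. Report the between-arm difference with its 95% CI at all four visits, and show these in the planned graph. Keep weeks 12 and 24 as the tested visits. Label weeks 4 and 8, in 8.1.2 as well, as estimates without a claim of significance, so that the number of HECSI tests stays at two.

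This is a small change of method and should be presented as one: section 10 mentions mixed models only conditionally, for missing data, and 10.2 does not plan one for HECSI. The model uses the early scores of patients who leave at week 12. It is valid if the missing scores are explained by what was observed, which remains an assumption.

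The cost is a change of wording, a little more analysis work and two more secondary estimates to report. No new data are needed. A model-based analysis also gives up the simple Mann-Whitney fallback, so the text should require a residual check, with a transformation if HECSI is skewed.

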##### **8.4.1 Specific criteria for withdrawal**

- Evidence of pregnancy
- Occurrence of serious adverse events
- Lack of efficacy at 12 weeks, defined as no improvement assessed by the PGA (at least 1 step improvement is necessary to continue treatment after 12 weeks)
- Use of prohibited concomitant therapy, or a need for their use
- The need for more than 3 courses of rescue medication
- Anaphylactic reaction or other severe systemic reaction to study drug intake
- Diagnosis of malignancy during study, excluding non-metastatic cutaneous squamous cell or basal cell carcinoma and/or localized carcinoma in situ of the cervix
- Any infection that is opportunistic and other infections whose nature or course may suggest an immunocompromised status
- Administration of a living vaccine
- Severe laboratory abnormalities including:
  - ALAT and/or ASAT values > 300% of the upper limit of normal
  - Lowered full blood count indicating a possible (developing) myelosuppression (to be determined by investigator or treating physician)
  - Triglycerides > 9 mmol/l
- Intercurrent severe illness or major surgery
- Protocol violations or if the requirements of the protocol are not respected
- Patient lost to follow up

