### **8.6 Follow-up of subjects withdrawn from treatment**

Subjects withdrawn from treatment will continue to be treated at our center, outside the study. All efforts will be made to report the observations for the reason(s) for premature withdrawal and the time of occurrence. If an adverse event is the reason for withdrawal, the physicians of our department will administer therapy as clinically indicated. All serious adverse events and those adverse events for which the relationship to the study drug is plausibly related will be followed up until they have returned to baseline status or stabilized.

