## 10. STATISTICAL ANALYSIS

This trial is designed to demonstrate a superior response to azathioprine compared to alitretinoin in the treatment of severe chronic non-hyperkeratotic hand eczema. Response to treatment is defined as an improvement of  $\geq 2$  steps on the Physician Global Assessment (PGA) developed by Ruzicka et al (8,9) at 24 weeks of treatment.

All analysis will be based on the intention-to-treat principle to guard against attrition bias. Subjects might not only withdraw because the study drug works insufficient, they might also withdraw when their hand eczema is cured.

Missing values will be handled in a way that is dependent on assumptions about the missing data. If the extent and pattern of missing data is known (e.g. missing at random (MAR), missing completely at random (MCAR), missing not at random (MNAR)), an analysis will be chosen that is valid under a plausible assumption about the missing data (probably mixed models). This is according to a strategy proposed by White et al. (28)

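### Time to response: a standard Kaplan-Meier analysis would censor week-12 non-improvers informatively and overstate response at week 24; section 10.2 should keep them at risk as non-responders

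*Protocol*

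**What the plan says.** Section 10.2 fixes the method for time to first response, a PGA improvement of at least two steps: "This will be analysed using a Kaplan-Meier product limit estimator". It adds: "For comparison between the alitretinoin and azathioprine group the Log-rank test will be used".

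Section 8.1.2 limits when a response can be seen: "This is only measured at control visits so possible outcome is limited to 4, 8, 12 and 24 weeks".

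Section 8.4.1 lists among the withdrawal criteria: "Lack of efficacy at 12 weeks, defined as no improvement assessed by the PGA". It explains that "at least 1 step improvement is necessary to continue treatment after 12 weeks".

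Section 8.6 says what follows: "Subjects withdrawn from treatment will continue to be treated at our center, outside the study". It plans follow-up of the reason for withdrawal and of adverse events, but no further PGA.

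The general part of section 10 says "All analysis will be based on the intention-to-treat principle to guard against attrition bias". It leaves the treatment of missing values to a later choice that depends on the missing-data assumption, with mixed models as the likely option. It gives no censoring rule for time to response.

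**The concern.** Kaplan-Meier and the log-rank test require that a patient censored at a given time has the same later chance of the event as those still at risk. The week-12 rule breaks this, because it selects on the same scale that defines the event. A patient withdrawn under it has gained no step and needs two. A patient who stays and has not yet responded has, under the rule, gained exactly one step, since two would already count as a response. If the first group is censored, the estimator gives it the week-24 response chance of the second.

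At stake are the level of the response curve after week 12 and, if the arms lose different shares of patients at week 12, the size and power of the log-rank test. Time to response is the first secondary objective in section 2.

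**Working it through.** **What the plan's figures give.** The protocol states no figure for time to response. Its response rates come from section 4.4: 33% for alitretinoin and 60% for azathioprine. The section 4.4 sample size reproduces closely. The uncorrected two-proportion formula gives 53 per arm against the stated 52, power at 52 per arm is 79.7%, and 52/0.9 rounds up to 58 per arm.

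**Assumed inputs.** The protocol gives neither the share of patients with no improvement at week 12 nor the timing of responses. Let c be the share responding by week 12, e the share first responding at week 24, and w the share withdrawn at week 12 for no improvement. Withdrawn patients are taken never to respond.

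**Formulas.**
- Kept at risk as non-responders: response by week 24 = c + e.
- Censored at week 12: response by week 24 = 1 − (1 − c)(1 − e/(1 − c − w)).

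**Level of the curve, with 60% of responses by week 12.**
- Alitretinoin: c = 0.6 × 0.33 = 0.198 and e = 0.132. With w = 0.10: 1 − 0.802 × (1 − 0.132/0.702) = 0.349.
- Azathioprine: c = 0.6 × 0.60 = 0.36 and e = 0.24. With w = 0.10: 1 − 0.64 × (1 − 0.24/0.54) = 0.644.

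| Arm | Kept at risk | w = 5% | w = 10% | w = 20% | w = 30% |
|---|---|---|---|---|---|
| Alitretinoin | 33% | 33.9% | 34.9% | 37.4% | 40.9% |
| Azathioprine | 60% | 62.0% | 64.4% | 70.9% | 81.2% |

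With 50-75% of responses by week 12 and w from 5% to 30%, the excess runs from 0.6 to 9.3 points for alitretinoin and from 1.5 to 22.5 points for azathioprine. The upper end for azathioprine is not a forecast: w = 30% would mean that three quarters of its 40% non-responders showed no improvement at week 12.

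**Effect on the comparison.** Censoring multiplies the week-24 response chance among those at risk by (1 − c)/(1 − c − w). The log-rank test shifts when this factor differs between arms.

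With equal true response in both arms, 58 per arm and two-sided 5%, simulated rejection rates are:

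| Withdrawn at week 12 | True response | Censored | Kept at risk |
|---|---|---|---|
| 20% v 20% | 33% | 5.2% | 5.3% |
| 25% v 10% | 45% | 7.2% | 5.0% |
| 30% v 10% | 45% | 9.3% | 4.9% |
| 40% v 5% | 45% | 21% | 5.3% |

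These use 20,000 runs, with responses split 10/20/30/40% over weeks 4/8/12/24. For 30% v 10%, c = 0.6 × 0.45 = 0.27, so the factors are 0.73/0.43 = 1.70 and 0.73/0.63 = 1.16. With 40% true response and a 10-point gap (30% v 20%, or 25% v 15%), rejection is 6-7%.

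At the planned 33% v 60%, power can move either way:
- 30% v 10% withdrawn: factors 0.802/0.502 = 1.60 and 0.64/0.54 = 1.19. Alitretinoin is raised more, and power is 68% censored against 82% kept.
- 20% v 20% withdrawn: factors 0.802/0.602 = 1.33 and 0.64/0.44 = 1.45. Azathioprine is raised more, and power is 88% against 83%.

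**A case where the contrast hardly moves.** Take c = 0.20 and 0.40, e = 0.13 and 0.20, and about one third of each arm's non-responders withdrawn (w = 0.22 and 0.13). The curves read 37.9% and 65.5%. With about half withdrawn (w = 0.335 and 0.20) they read 42.4% and 70.0%. Both curves are too high, but the gap is 27.6 points each time against a true 27.0.

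**The case against.** The strongest reply is that the protocol nowhere says these patients are censored. It names an estimator and a test, and censoring rules for a secondary endpoint often sit in an analysis plan, which is not at hand. Section 10 applies intention to treat to every analysis, with attrition bias in mind, and acknowledges withdrawal for insufficient effect. Keeping these patients at risk would fit that principle, and the planned log-rank test can be run on such data. It is right that censoring is an inference and that the named method can be kept. But a named method meets a written withdrawal rule that breaks its assumption, and neither the intention-to-treat sentence nor mixed models says how these patients enter a Kaplan-Meier risk set.

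A reader might also infer more than the protocol supports:

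- **That the comparison is biased in a known direction, with alitretinoin inflated most.** No section predicts which arm will have more non-improvers at week 12. Section 6.1 says azathioprine can take weeks to months to act, which could point the other way. In the last case above, alitretinoin loses more patients yet is inflated slightly less (4.9 v 5.5 points).
- **That type I error is seriously inflated.** A rate of 17% (52 per arm, 4,000 runs) needs 40% v 10% withdrawn with identical response in both arms.
- **That the tied visit times invalidate the log-rank test.** In the simulations, with events only at visits, the test holds about 5% once patients are kept at risk.
- **That disagreement with the primary proportion proves the fault.** The curve counts first response at any visit, the primary endpoint counts response at week 24, and a relapse separates them under any censoring rule.

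Finally, counting withdrawn patients as non-responders is itself a choice of estimand. It is reasonable here, but it should be stated.

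**Conclusion.** The point holds in a limited form. If time to response is run as a standard Kaplan-Meier analysis, the week-12 rule makes the censoring informative, and the week-24 response is overstated whenever patients are withdrawn under that rule and others respond later. At 10% withdrawn the excess is about 2 points for alitretinoin and 4 for azathioprine, and it grows with the share withdrawn.

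The log-rank test is distorted only so far as week-12 withdrawal differs between arms for reasons other than response. With equal response, type I error is about 5% for equal withdrawal and about 6-10% for gaps of 10-20 points.

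These sizes rest on assumed withdrawal shares and response timing, and on withdrawn patients counting as non-responders. The direction cannot be predicted from the protocol. Weeks 4-12 of the curve, the primary endpoint and its sample size are unaffected. The change is worth making before data are seen, in proportion to a secondary endpoint.

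**What to change.** Add to section 10.2 that patients withdrawn for lack of efficacy at week 12 stay in the risk set as non-responders and are censored at week 24, so that the curve shows the cumulative incidence of response. Apply the planned log-rank test to that data set. Report the analysis with censoring at withdrawal as a sensitivity analysis, and say how withdrawals for other reasons are handled. A discrete-time model on the four visits is optional.

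This is a wording change. It needs no extra visits or patients and leaves the week-12 withdrawal rule as it is. The cost is somewhat lower reported response curves, and an explicit commitment to counting these withdrawals as non-response.
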